# High flow nasal oxygen after bariatric surgery (OXYBAR), prophylactic post-operative high flow nasal oxygen versus conventional oxygen therapy in obese patients undergoing bariatric surgery: study protocol for a randomised controlled pilot trial

**DOI:** 10.1186/s13063-018-2777-2

**Published:** 2018-07-27

**Keywords:** Obesity, Bariatric surgery, High flow nasal oxygen, Post-operative respiratory complications, Electrical impedance tomography

## Abstract

**Background:**

The incidence of obesity is increasing worldwide. In selected individuals, bariatric surgery may offer a means of achieving long-term weight loss, improved health, and healthcare cost reduction. Physiological changes that occur because of obesity and general anaesthesia predispose to respiratory complications following bariatric surgery. The aim of this study is to determine whether post-operative high flow nasal oxygen therapy (HFNO_2_) improves respiratory function and reduces the incidence of post-operative pulmonary complications (PPCs) in comparison to conventional oxygen therapy in these patients.

**Method:**

The OXYBAR study is a prospective, un-blinded, single centre, randomised, controlled pilot study. Patients with body mass index (BMI) > 30 kg/m^2^, undergoing laparoscopic bariatric surgery, will be randomised to receive either standard low flow oxygen therapy or HFNO_2_ in the post-operative period. The primary outcome measure is the change in end expiratory lung impedance (∆EELI) as measured by electrical impedance tomography (EIT). Secondary outcome measures include change in tidal volume (∆Vt), partial arterial pressure of oxygen/fraction of inspired oxygen (PaO_2_/FiO_2_) ratio, incidence of PPCs, hospital length of stay and measures of patient comfort.

**Discussion:**

We hypothesise that the post-operative administration of HFNO_2_ will increase EELI and therefore end expiratory lung volume (EELV) in obese patients. To our knowledge this is the first trial designed to assess the effects of HFNO_2_ on EELV in this population. We anticipate that data collected during this pilot study will inform a larger multicentre trial.

**Trial registration:**

Australian New Zealand Clinical Trials Registry (ANZCTR), ACTRN12617000694314. Registered on 15 May 2017.

**Electronic supplementary material:**

The online version of this article (10.1186/s13063-018-2777-2) contains supplementary material, which is available to authorized users.

## Background

Obesity, defined as a body mass index (BMI) > 30 kg/m^2^, has almost doubled since 1980, with more than 671 million people worldwide now classified as obese [1, 2]. Health problems associated with obesity impact on quality of life and impose a significant cost burden to health services. Being obese is associated with a higher frequency of cardiovascular disease [3], of metabolic diseases such as type II diabetes mellitus [4], of respiratory morbidity secondary to obstructive sleep apnoea (OSA) and obesity hypoventilation syndrome (OHS) [5]. In Australia, health expenditures of those with a BMI between 30 and 35 kg/m^2^ are 19% higher than those of a normal-weight individual. This increases to 51% in those with a BMI > 35 kg/m^2^ [6]. Overall, the total financial cost of obesity is estimated to be 8.3 billion AUD [7].

Obesity is difficult to treat. Diet, exercise and medications are only modestly effective in aiding weight loss [8]. In selected individuals, bariatric surgery may offer a means of achieving long-term weight loss, improved health outcomes and a reduction in healthcare spending [9–11]. However, bariatric procedures are complicated by the additional risks associated with anaesthesia and surgery in the obese patient. Obesity and its associated co-morbidities, have been shown to increase the rate of post-operative myocardial infarction, peripheral nerve injury, wound and urinary tract infection and the requirement for re-intubation [12].

The evidence that obesity increase the incidence of PPCs is mixed. A retrospective observational study by Baltieri et al. described a 37% prevalence of atelectasis in obese patients following bariatric surgery [13]. Several studies have identified obesity as an independent risk factor for post-operative respiratory complications [14–17], while others have failed to find an association [18–20]. However, respiratory complications are not infrequent amongst the general surgical population and have been shown to increase hospital length of stay and mortality [21].

Physiological and pathological changes that occur because of obesity adversely affect both lung mechanics and gas exchange. First, there is a reduction in total respiratory system compliance and an increase in airway resistance [22, 23]. Increased mass loading on the chest wall, cephalad displacement of the diaphragm and an increase in pulmonary blood flow contribute to this [24, 25]. Taken together, these changes lead to higher work of breathing [22] and a tendency toward shallow, rapid tidal volumes (Vt) [26]. Second, breathing at a lower Vt leads to a reduction in end expiratory lung volume (EELV) [27], increasing the potential for atelectasis and ventilation/perfusion mismatching [28, 29]. The physiological alterations outlined above are further exacerbated when the patient is in the supine position and by general anaesthesia (GA), with functional residual capacity (FRC) falling by up to 50% on induction [30]. This reduction persists longer into the post-operative period in obese compared to non-obese individuals [16].

### High flow nasal oxygen therapy

High flow nasal oxygen (HFNO_2_) therapy was first shown to be an effective treatment for acute respiratory failure in the paediatric and neonatal populations [31, 32]. Recently, it has gained popularity as a therapy in adult patients, with an expanding list of clinical applications [33].

High flow nasal cannulae (HFNC) are designed to deliver an air/oxygen blend at a predetermined fraction of inspired oxygen (FiO_2_). The heating and humidification of inspired gases allows for higher flow rates to be tolerated when compared to conventional oxygen delivery devices. Flow rates of up to 70 L/min can be achieved. The process of heating and humidification also reduces mucosal drying, improves muco-ciliary clearance and reduces energy expenditure and work of breathing [34]. Higher flow rates reduce room air entrainment during inspiration and flush expired air from the upper airway during expiration, leading to the delivery of higher and more consistent FiO_2_ [34]. There is additional evidence to suggest that the higher flow rates achievable with HFNC generate a degree of positive airway pressure, which increases end expiratory lung volume (EELV) and alveolar recruitment [35, 36].

### Electrical impedance tomography

Electrical impedance tomography (EIT) is a non-invasive, radiation-free, functional imaging modality [37]. It uses changes in bio-impedance across lung tissue during the respiratory cycle to provide information on ventilation distribution, lung volumes, and regional lung mechanics [38]. EIT has been successfully validated against several other imaging and measurement modalities and strong linear correlation between the change in end expiratory lung impedance (EELI) and the EELV has been described [39–42].

### Rationale for the study

A rise in the incidence of obesity has resulted in a rapid escalation in the number of bariatric procedures being carried out worldwide. Obese patients undergoing surgery of any kind are at a higher risk of developing post-operative atelectasis secondary to the physiological and pathological changes outlined above. Study data from our group suggests that the use of HFNO_2_ when compared to low-flow oxygen devices significantly increases EELI (which in turn is associated with an increase in EELV). This relationship appears to be enhanced at higher BMIs. In the study of Corley et al., a mean increase in EELI of 1517 ± 46.6 units was associated with a reduction in respiratory rate, an increase in P/F ratio, and a reduction in a standardised dyspnoea score [35].

We propose to carry out a randomised, controlled pilot study to evaluate the effects of post-operative HFNO_2_ therapy on EELV in the obese population undergoing laparoscopic weight reduction surgery. Data gathered will be used to explore the mechanism of action of HFNO_2_ therapy in this setting and to inform the design of a larger trial with a patient-centred primary outcome.

## Methods/design

### Objectives and design

#### Research hypothesis

In obese adult patients undergoing laparoscopic bariatric surgery, prophylactic post-operative HFNO_2_ therapy will increase EELI and therefore EELV, improve respiratory function and reduce the incidence of PPCs.

#### Study design

This is a prospective, un-blinded, single centre, randomised, controlled pilot study, with an allocation ratio of 1:1. This protocol has been designed in accordance with the Standardised Protocol Items: Recommendations for Interventional Trials (SPIRIT) guidelines and checklist [43] (Additional file 1). A schedule for enrolment, intervention and assessment (SPIRIT figure) is outlined in Fig. 1.

**Fig. 1 Fig1:**
[figure not shown]
A schedule for enrolment, intervention and assessment (Standardised Protocol Items: Recommendations for Interventional Trials (SPIRIT) figure). HFNO_2_, high flow nasal oxygen; EIT, electrical impedance tomography; PaO_2_/FiO_2_, arterial partial pressure of oxygen/fraction of inspired oxygen; PaCO_2_, arterial partial pressure of carbon dioxide

#### Study objectives

The primary objective of this study is to determine the effect of post-operative HFNO_2_ on EELV in obese patients undergoing bariatric surgery. The primary outcome measure is ∆EELI between baseline and 6 h post allocation.

Secondary objectives are to determine the effect of HFNO_2_ on oxygenation and respiratory parameters, the incidence of PPCs, hospital length of stay and patient comfort. In addition, this study will provide important data (protocol feasibility, estimates of post-operative complications) and experience (consent and screening procedures, refining data collection processes), which will be used to design a large trial powered to detect differences in patient centred outcomes.

#### Study setting

The OXYBAR study will take place at St Andrews War Memorial Hospital (SAWMH), Brisbane, Australia. The hospital provides tertiary level care in a 250-bed facility, with a 15-bed Intensive Care Unit (ICU).

#### Sample size and study duration

This is a pilot study and as such no formal power calculation has been made. A convenience sample of 50 patients has been chosen based on anticipated recruitment rates and a feasible study duration.

Given our institution’s current workload, approximately two patients per week will meet the inclusion/exclusion criteria. Allowing for a 50% consent rate, and 10% loss to long-term follow up, recruitment could be completed in 54 weeks. Given the final follow up occurs 6 weeks post-operatively, data collection may be completed by week 60. Data analysis and write up of results will take an additional 12 weeks. Therefore, completion of the study is expected within an 18-month time frame.

#### Allocation

Randomisation will be achieved using a computer-generated random number table, with an allocation ratio of 1:1. Allocation concealment will be maintained using sequentially numbered sealed opaque envelopes. Envelopes will be prepared by an independent person. Each envelope will contain a unique patient identifier code and will allocate the participant to either the intervention group (HFNO_2_) or the control group (standard oxygen therapy). Randomisation will occur post-operatively on admission to the ICU. The theatre team will be blinded to the allocation. Due to the research design, neither the individual collecting data nor the patient can be blinded to treatment allocation.

### Participants, interventions and outcomes

#### Screening and consent

Patients opting to undergo laparoscopic surgery for weight reduction will be identified by the surgical team in the surgical outpatient clinic. Those that meet the eligibility criteria outlined in Table 1 will be given written information regarding the study at this time.

**Table 1 Tab1:** Eligibility criteria

Inclusion criteria	Exclusion criteria
Age ≥ 18 years	Age < 18 years
BMI ≥ 30 kg/m^2^	Refusal to consent
Undergoing a laparoscopic procedure for weight reduction	Any contraindication to HFNO_2_
Informed consent obtained	Chest circumference too large for EIT belt
	Severe chronic lung disease
	Preoperative hypoxia SpO_2_ < 92%

*BMI* body mass index, *HFNO*_*2*_ high flow nasal oxygen, *EIT* electrical impedance tomography, *SpO*_*2*_ peripheral oxygen saturation

On the morning of surgery, patients will be approached by a member of the study team and informed written consent will be sought. The right of the patient to refuse to participate without giving reasons will be respected. All participants are free to withdraw at any time from the study without giving a reason and without prejudicing further treatment.

#### Pre-operative management

Pre-operative management of the patients in both groups will be consistent with current surgical best practice and at the discretion of the responsible surgeon. The study period will begin after informed consent is secured.

#### Control group

The control group will continue to receive supplemental oxygen. Oxygen will be titrated to maintain peripheral oxygen saturations (SpO_2_) ≥ 95%. If, after an initial period of stabilisation in the ICU, patients consistently achieve or exceed the SpO_2_ target, therapy may be titrated downwards (including the use of conventional nasal cannulae). A minimum of 2 L/min of supplemental oxygen will be maintained for the duration of the study period.

#### Intervention group

Patients will be managed with supplemental oxygen delivered via HFNC (Airvo™ 2, Fisher & Paykel, New Zealand) at an initial FiO_2_ of 0.5 and a flow rate of 50 L/min. Oxygen therapy will then be titrated to maintain SpO_2_ ≥ 95%. A constant flow rate of 50 L/min will be maintained for the duration of the study period.

#### Outcome measures

Primary and secondary outcome measures are summarised in Table 2. The primary outcome measure is ∆EELI from baseline to 6 h post-return to ICU.

**Table 2 Tab2:** Summary of primary and secondary outcome measures

Phase	Outcome measure	Timing	
Day 0	Change in end expiratory lung impedance (∆EELI)	6 h	Primary outcome
Day 0	Change in end expiratory lung impedance (∆EELI)	15 min, 60 min, and 3 h	Secondary outcomes
	Change in Tidal impedance variation (∆VARt)	0, 60 min, 3 h, and 6 h	
	Change in oxygenation (PaO_2_/FiO_2_)		
	Change in arterial CO_2_ (PaCO_2_)		
	Change in respiratory rate		
	Change in modified Borg dyspnoea score		
	Requirement for escalation of O_2_ therapy		
Discharge	Length of ICU stay	Day 2–3	
	Re-admission to ICU		
	Length of hospital stay		
	Diagnosis of a respiratory complication		
Follow up	Hospital re-admission	Week 6	
	Diagnosis of a respiratory complication		

*EELI* end expiratory lung impendence, *PaO*_*2*_*/FiO*_*2*_ arterial partial pressure of oxygen/fraction of inspired oxygen; *PaCO*_*2*_ arterial partial pressure of carbon dioxide

### Data collection, quality and management

#### Time points

Pre-operative refers to the period after recruitment, but before surgery and before randomisation. Pre-operative data collected include:Patient demographics (age, gender, height and weight)Modified Borg dyspnoea score of 0 = no dyspnoea to 10 = maximal dyspnoea [44]Co-morbidity data (including smoking history)Baseline physiological parameters (heart rate, blood pressure, respiratory rate, peripheral oxygen saturation)

Baseline refers to the period after surgery and before randomisation. All patients will return from theatre after being extubated by the responsible anaesthetist and after receiving 6 L/min of 0_2_ via a Hudson mask. Baseline data collected include:EIT file recordingArterial blood gas analysis▪ Arterial partial pressure of oxygen (Pa0_2_)▪ Arterial partial pressure of carbon dioxide (PaC0_2_)▪ Calculated Pa0_2_/Fi0_2_ ratioPhysiological parameters (as above)Modified Borg dyspnoea score (as above)Pain score▪ Numerical scale where 0 = no pain and 10 = maximal painOperative data▪ Type of operation preformed▪ Duration of operation▪ Any related complicationsGeneral anaesthesia data▪ Type of anaesthesia administered▪ Amount of analgesia given▪ Any related complications

After baseline data have been recorded, randomisation will occur - T0 refers to this point.

T15, T60 and T3 refer to 15 min, 60 min, and 3 h after T0, respectively. Data collected include:EIT file recordingArterial blood gas analysisPhysiological parametersModified Borg dyspnoea scorePain score

T6 refers to 6 h after T0. Data collected include all data from the above time point in addition to:Data on clinical course, need for oxygen titration or escalation of therapy

Discharge refers to the day of discharge from the hospital. Discharge data collected include:Hospital length of stayPhysiological parametersData on clinical course, need for oxygen titration or escalation of therapyICU re-admissionData on the incidence of PPCs

PPCs are defined in this study as any pulmonary abnormality, disease or dysfunction that adversely affects the clinical course of a patient in the post-operative period. This includes mild, moderate or severe respiratory failure, acute respiratory distress syndrome (ARDs) new onset bronchospasm, new pulmonary infiltrates on chest x-ray, pulmonary infection and the presence of new plural effusions, atelectasis, cardiopulmonary oedema or pneumothorax [45].

Six weeks refers to follow up post discharge at the surgical outpatient clinic. Six-week data collected include:Need for hospital re-admissionAny respiratory complications requiring medical intervention

#### EIT data measurement

EIT measurements will be performed with the PulmoVista® 500 (Dräger Medical, Lubeck, Germany). Discreet files will be acquired over a 5-min period, with a frame rate of 20 frames/second. Files will be automatically saved to the device hard drive. Analysis will take place off-line using Dräger review software V5.1 and then downloaded using Microsoft Excel (Microsoft, Redmond, USA).

All EIT measurements will be recorded with the patient in bed inclined to 30–45°. EIT belt placement will be standardised to the 4th–5th intercostal space, below the breast tissue where appropriate. Belt position will be marked with surgical ink to ensure minimal displacement between readings.

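### Bed angle may vary from 30 to 45 degrees between a patient's EIT readings and is not a listed data item, and it is unclear whether EELI extraction is blinded

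*Protocol article*

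**What the plan says.** The section EIT data measurement sets the posture: "All EIT measurements will be recorded with the patient in bed inclined to 30–45" degrees. It fixes the belt more tightly, at a named intercostal level, and adds: "Belt position will be marked with surgical ink to ensure minimal displacement between readings". On recording and processing it says: "Discreet files will be acquired over a 5-min period, with a frame rate of 20 frames/second", and "Analysis will take place off-line using Dräger review software V5.1", followed by download to a spreadsheet. It does not name the person who does this step.

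The section Outcome measures defines the endpoint: "The primary outcome measure is ∆EELI from baseline to 6 h post-return to ICU". Under Time points, the baseline EIT file precedes randomisation, and later files follow at T15, T60, T3 and T6. The items listed with each file are blood gases, physiological parameters (heart rate, blood pressure, respiratory rate, oxygen saturation), dyspnoea score and pain score. Bed angle is not among them.

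On blinding, the section Allocation says that "neither the individual collecting data nor the patient can be blinded to treatment allocation". Statistical methods assigns all analyses to an independent biostatistician who is blinded to allocation.

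**The concern.** A within-patient change score is only as clean as the repeatability of its two readings. The authors acted on this for the belt, which is marked so that it returns to the same place. They did not do so for posture: a patient read at 30 degrees at baseline and 45 degrees at T6 complies fully with the protocol. As angle is not a listed item, the listed data would not show that this had happened or allow the analysis to examine it.

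Baseline angle is set before randomisation and cannot depend on arm. The later angles are set after allocation, while the staff collecting data know the arm. Any arm-related habit in positioning would pass into the treatment contrast.

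The second matter is extraction. The bedside collector cannot be blinded, but someone reading saved files off-line can be. This step produces the primary endpoint, so whether it is blinded should be plain.

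**Working it through.** The article has no figure to reproduce on this point: the sample of 50 is a convenience sample without a power calculation. The steps below show what can and cannot be said about size.

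**1. Angle change allowed.** The band is 45 − 30 = 15 degrees, so the largest within-patient shift is 15 degrees. If the angle is independent and uniform over the band at each reading (an assumption), the SD of the baseline-to-T6 difference is 15/√12 × √2 = 15/√6 = 6.12 degrees.

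**2. Inputs the article does not give.** It states no EELI units per degree of inclination. It cites an earlier mean EELI increase of 1517 ± 46.6 units without saying whether the second number is an SD or a standard error, so no SD of the change can be taken from it. Both inputs must be assumed.

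**3. Noise.** With k units per degree, posture adds an SD of 6.12 × k. For illustration take 25 per arm, a between-arm difference of 1517, a two-sided 5% test of two means (simpler than the planned mixed model), and an SD of 1500 without posture shifts. The total SD is √(1500² + (6.12k)²).

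| k (assumed) | Added SD | Total SD | Power | Bias if the arms differ by 5 degrees at T6 |
|---|---|---|---|---|
| 0 | 0 | 1500 | 0.947 | 0 |
| 25 | 153 | 1508 | 0.945 | 125 |
| 50 | 306 | 1531 | 0.939 | 250 |
| 100 | 612 | 1620 | 0.912 | 500 |
| 200 | 1225 | 1936 | 0.791 | 1000 |

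With a starting SD of 2500, power runs from 0.574 at k = 0 to 0.487 at k = 200.

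A milder assumption is that 15 degrees is worth 10% to 40% of 1517, that is 152 to 607 units, or about 10 to 40 units per degree. The added SD is then 6.12/15 = 0.408 times 152 to 607, or 62 to 248 units. At the top of that range the total SD is √(1500² + 248²) = 1520, a rise of 1.4%.

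**4. Bias.** If shifts are unrelated to arm, the expected bias is zero. Because baseline angle precedes randomisation, the arm difference in angle change is expected to equal the arm difference in T6 angle. A 5-degree difference, itself hypothetical, gives 5k: 51 to 202 units under the milder assumption (3% to 13% of 1517) and 250 to 1000 units at k = 50 to 200. For posture alone to equal 1517 units, a full 15-degree arm difference would need k = 1517/15 = 101.

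The two assumed ranges for k (10 to 40, and 50 to 200) do not overlap, and the article does not help to choose between them.

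**5. Extraction.** EIT data measurement says "Analysis will take place off-line using" the vendor's review software, with no reader named. Statistical methods gives all analyses to the blinded statistician. Data quality gives data collection to the study lead and team. These sections do not settle which role extracts EELI, or whether that person knows the arm.

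**The case against.** The article does standardise posture: one bounded semi-recumbent band applies to both arms, alongside a fixed and marked belt level. The Background remark that the respiratory changes of obesity are "further exacerbated when the patient is in the supine position" concerns lying flat, which the band excludes, and says nothing about 30 against 45 degrees. It makes posture a reasonable thing to control in these patients but is not evidence of an effect within the band. Drift unrelated to allocation is only noise, and under the milder assumption that noise is small. This is a pilot, and no stated sample size or error rate changes. All of that stands.

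A reader might infer that EELI is extracted unblinded and that the statistician merely receives finished numbers. The article does not say so: the blinded remit may include extraction. Nor does it describe any choice of breaths or segments within the 5-minute file. Segment and artefact rules, and possibly the angle field itself, may sit in the full protocol, the CRF or the operating procedures that Data quality mentions, so their absence from an article is not an error.

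These arguments do not remove the stated posture rule, which leaves the angle free between the two readings that form the primary outcome.

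**Conclusion.** The point holds as a gap in measurement standardisation that is cheap to close. It does not show that the primary result would be biased. The posture rule permits shifts of up to 15 degrees within a patient. These enter the primary change score as noise, and as bias only if positioning after allocation differs by arm. Unblinded bedside staff make that possible, but nothing in the article suggests that it happens.

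The size cannot be estimated from the document. The illustrations run from negligible to material, depending wholly on an assumed effect per degree, an assumed SD and, for bias, an assumed arm difference. Blinding of extraction is unclear rather than shown to be absent. The pilot is meant to inform a larger trial, so avoidable variance in its endpoint is worth removing.

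**What to change.** - Within the protocol's own 30–45 degree band, record each patient's bed angle at the baseline EIT reading, reproduce it at T15, T60, T3 and T6, and log the angle on the CRF each time.
- Store the EIT files under codes that hide the arm, and extract EELI before the codes are linked to allocation. State which role does the extraction and that it is blinded.

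The cost is one CRF field per reading, coded file names, and slight bedside and filing effort. No extra staff or procedure is needed. The article reports recruitment from April 2017 and still describes the trial as recruiting. The angle rule can therefore help only readings not yet taken, whereas coded extraction can cover every saved file not yet read.
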